#### Health economic analysis

This trial has been designed to be inexpensive to run but there will be some cost associated with training sessions and some staff time associated with completing the checklists, as well as addressing the dental needs of the service users. It is anticipated that more dental appointments will be made in the intervention teams, and the cost of these to the service user, EIP team and NHS dentist should be calculated.

There are two arms to this trial; the dental intervention delivered alongside standard care or standard care alone. The dental intervention includes a one-off session of dental awareness training provided to care co-ordinators within individual EIP teams, a dental information sheet provided to service users and a checklist that will be completed with each service user. This would thus lead to resource use including but not limited to planning, formulation, training and implementation of the dental awareness training as well as staff contact time for completion of checklists. Increase in level of staff input (contact time) as well as additional dental visits will need to be recorded. The cost-effectiveness analysis will be from the perspective of the National Health Service (NHS) in England, as we will plan on looking at the incremental cost-effectiveness ratio.

As this is the first pragmatic trial of oral health advice for people with serious mental illness, there is an uncertainty as to the magnitude of difference in effectiveness in the two arms of the trial. Should there be a statistically significant difference between the two groups, we would proceed with a full economic evaluation including cost-effectiveness analysis and cost-utility analysis (possible as the OIDP will be administered to a sample of 100 patients). However, should there be no difference, we would conduct a partial economic evaluation in the form of a cost analysis. The primary outcome measure for this trial is number of visits to the dentist within 12 months of exposure to the checklist.

Data regarding dental visits from a subsample of 100 service users will be obtained at the end of the study period and the difference in dental visits between the two groups can be used in calculation of the incremental cost-effectiveness ratio. The effectiveness data could also be calculated as a potential savings to the NHS for varied dental treatment due to early detection of dental pathology.

The estimated unit cost of the intervention and standard care will be based on 2012 to 2013 reimbursement rates for the NHS. The costs will be determined by multiplying the resources used and their volumes by the estimated cost per unit. A cost-effectiveness analysis is a form of economic evaluation that compares the relative costs and effects of two alternative options. In this trial the incremental cost-effectiveness ratio will be the ratio wherein the denominator would be patients keeping their dental appointments during the year (or Decayed, Missing and Filled Teeth (DMFT) rates if available) and the numerator would be the cost associated with the health gain. Based on data obtained, a detailed probabilistic sensitivity analysis will be carried out in order to get a range of incremental cost-effectiveness ratios.

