#### Sample size

No previous trials exist [19]. It is, therefore, difficult to determine the number of people that need to be recruited to generate clinically significant data regarding the effect of an oral health advice intervention on the oral health of people with a serious mental illness. As we designed the study in consultation with clinicians and service users, we tried to gain an impression of the size of difference that would cause a change in practice. We did not formally record these estimates, but consensus suggested a range of between 10% to 20%. We estimate the sample size for the mid-way point (Table 1).

**Table 1 T1:** Sample size needed to detect an absolute difference of 15% in the proportion of visits to a dentist (α = 5%, power = 80%)

**Standard care, %**	**Dental intervention, %**	**Non-cluster N (total)**	**Multiplied by design effect**	**Adjusted for 20% dropout**
5	20	176	334	418
10	25	226	430	538
15	30	268	510	638
20	35	302	574	718
25	40	330	628	785
30	45	352	670	837
35	50	366	696	870

Complicating this further is that this is a cluster trial so the EIP teams will be randomised as a whole team rather than at the individual patient level. Intraclass correlation coefficient (ICC) in cluster trials are difficult to estimate if no previous studies exist and to not take clustering into account would lead to ignoring the potential for a unit-of-analysis error [22-24]. Simply estimating that we will be able to randomise the people for whom the 10 teams provide care into two groups is not an accurate reflection of the power of the study. This has to be multiplied by a design effect to adjust for clustering. There are two levels of clustering within this trial, the EIP teams are the clusters that will be randomly allocated to receive the interventions but there are also clusters within the teams; the individual care co-ordinators. Non-cluster N was calculated using the Stata version 11 software (StataCorp, College Station, TX, USA) with alpha = 0.05, power = 0.80. The design effect (DE) was calculated considering patients clustered within each staff/team and each staff sees 10 patients (DE = 1+ (10–1)*0.1 = 1.9), with an intracluster coefficient of 0.1 as a best guess.

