Assuming that 5% of the service users who receive standard care visit a dentist, to then detect a 15% increase in the proportion of those who visit a dentist in the dental intervention arm with 80% power at 0.05 significance level, we need 176 service users for a single-centre trial, after adjusting for the cluster effect by multiplying this by the design effect, we need to recruit 334 service users. After further adjusting for 20% of service users lost to follow up, the final number of service users we need to recruit is 418. Other situations with various proportions of visits to a dentist in standard care are also presented in Table 1.

All these assumptions we have made in this power calculation may be correct or all may be incorrect. It is, at this point, quite impossible to say. As can be seen from the background, no studies have been undertaken in this area. There is no data to even guess what any effect may or may not be. This is a pioneering trial that will set a standard and will allow researchers in the future to have some benchmark off which to work.

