#### Follow-up

The trial team will prompt the intervention group care co-ordinators for the 12-month follow-up where dental checklists will be completed again for all service users. A total of 100 service users will be randomly selected from all teams and their care co-ordinators will be encouraged to ask them if contact from the trial team is acceptable regarding the Oral Impacts on Daily Performance (OIDP) measure as well as for collecting detailed data from their dentists (if they have visited a dentist within the previous 12 months). If it is not - no contact will be made. For this person, the trial is then over. The OIDP is a scale which assesses the impacts to which dental problems affect an individual’s life on a daily basis (see Additional file 4).

All service users who have indicated that contact from the trial team is acceptable will be contacted by an independent researcher and consent gained for conduct. For the OIDP information sheets will be given out and consent forms will be signed. The OIDP will then be administered as a short 20-minute interview by the researcher. For the detailed dental data, information sheets will be given out and consent forms will be signed. Dentists will then be contacted and information about recent dental treatment and current state will be requested Figure 1.

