### Outcomes

#### Primary outcomes

Number of service users who have visited a dentist within 12 months of exposure to the checklist as reported on the checklist.

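### The optional DMFT denominator for the ICER would be observed only among users who visited a dentist, which is the primary outcome, so the contrast is not randomised and could be biased in either direction

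*Protocol article*

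**What the plan says.** The Protocol article, Health economic analysis, defines the ICER with patients keeping their dental appointments during the year in the denominator, "or Decayed, Missing and Filled Teeth (DMFT) rates if available". This is the only mention of DMFT. It is not among the primary or secondary outcomes.

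The Follow-up section describes where clinical dental information comes from. "A total of 100 service users will be randomly selected from all teams", and their care co-ordinators ask whether the trial team may contact them, among other things for "collecting detailed data from their dentists (if they have visited a dentist within the previous 12 months"). For those who agree and consent, the dentist is approached and "information about recent dental treatment and current state will be requested". No examination by the trial, at baseline or at 12 months, is described.

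The primary outcome is "Number of service users who have visited a dentist within 12 months of exposure to the checklist as reported on the checklist". The Health economic analysis section expects the intervention to change this: "It is anticipated that more dental appointments will be made in the intervention teams". It also makes the full economic evaluation conditional on a statistically significant difference between the groups.

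**The concern.** Under the described procedure, whether a user has a DMFT value depends on whether that user visited a dentist. That is a post-randomisation event, and it is the event the intervention is meant to change. The wording about availability is therefore not a neutral safeguard: for this source, available means that the user attended.

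If the intervention works, the attenders in its arm are a mixture of people who would have gone anyway and people who went because they were prompted. The control attenders are only the first kind. Any difference in oral state between these two kinds of attender appears as a difference between arms, even if no tooth has been affected. Because the full evaluation is triggered by a significant difference, and the article names dental visits as the primary outcome, the ICER would be calculated precisely when attendance differs and this selection is active.

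There is a second, separate weakness. DMFT, read from its name as a sum, counts decayed, missing and filled teeth. Treating a decayed tooth moves it from one category to another and leaves the sum unchanged. Dental treatment obtained through extra visits would not register as the health gain that the ICER is meant to price.

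At stake is a cost-effectiveness figure whose denominator could be wrong in size or in sign.

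**Working it through.** **The plan's own figures.** The attendance rates come from the Sample size section and Table 1, so that table was checked first. "Assuming that 5% of the service users who receive standard care visit a dentist" gives the first row, 5% against 20%. A two-sided comparison of two proportions with continuity correction, "with alpha = 0.05, power = 0.80" (two-sidedness assumed), gives 176 in total. Then 176 × 1.9 = 334.4 and 334.4 / 0.8 = 418, as stated. All seven rows reproduce to rounding. The sample size is not in question here; only its rates are used.

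**Inputs.**
- From the document: 100 sampled users, and attendance from 5% against 20% up to 35% against 50%, always 15 points apart.
- Assumed: 50 sampled users per arm, all agreeing to contact; everyone who would attend under standard care would also attend under the intervention; no true effect on teeth.
- Assumed, because the article gives no figure: prompted attenders have a mean DMFT that differs from habitual attenders' by D, with D between −2 and +2.

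**Users with a dentist record** = 50 × attendance rate.

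**Share of intervention-arm attenders who were prompted** = 0.15 / (p + 0.15), where p is the control rate.

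**Spurious difference in mean DMFT, intervention minus control** = prompted share × D.

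| Control / intervention | Records, control | Records, intervention | Prompted share | D = +2 | D = 0 | D = −2 |
|---|---|---|---|---|---|---|
| 5% / 20% | 2.5 | 10 | 0.15/0.20 = 75% | +1.50 | 0 | −1.50 |
| 20% / 35% | 10 | 17.5 | 0.15/0.35 = 43% | +0.86 | 0 | −0.86 |
| 35% / 50% | 17.5 | 25 | 0.15/0.50 = 30% | +0.60 | 0 | −0.60 |

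A positive value looks like harm and a negative value like benefit. With a visit effect d in place of 0.15, the prompted share is d/(p + d), which rises with d. The bias therefore grows with the success of the intervention on its primary outcome.

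**Cross-check by another route.** Suppose a user attends when a normal latent propensity exceeds a threshold, and this propensity has correlation r with DMFT (assumed SD 4, no true effect). Mean DMFT among attenders shifts by 4 × r × φ(z)/p, where z is the threshold for attendance p. At 5% and 20%, φ(z)/p is 2.063 and 1.400. With r = −0.5 the arms differ by 4 × (−0.5) × (1.400 − 2.063) = +1.33, and with r = +0.5 by −1.33. At 35% and 50% the corresponding values are +0.52 and −0.52. The sign again depends on an input that the article does not supply.

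**Scale of missingness.** Over these rates, 50% to 95% of the sampled users in an arm have no DMFT because they did not attend, and the fraction observed differs between arms by the 15-point effect itself.

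**The case against.** The strongest reply is that little depends on this text. DMFT appears once, in a parenthesis, and only conditionally. The first-named denominator is kept appointments, and the same section says that the difference in visits can be used for the ICER. DMFT is not a listed outcome, and with two or three control records the option might simply lapse. All of this stands and limits the weight of the point. It does not remove it: the plan expressly permits the substitution, and at the upper rates of Table 1 there would be enough records for someone to carry it out.

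It can also be said that the Follow-up section never names DMFT, so its source is inferred. That is right. But the dentists' report on current state is the only source of clinical dental information the article describes.

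The section on missing data plans multiple imputation or a selection-bias model. It is written around users who leave early, not around a measure that is absent because no visit took place. With so few records and no baseline dental examination described, either method would rest almost wholly on its assumptions.

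On the index itself, an ICER uses the difference between arms, so a cumulative count could still differ through fewer new events. That is fair. The valid statement is that DMFT is insensitive to treatment over 12 months, not that it cannot differ between arms.

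Finally, a reader might infer that a DMFT-based ICER would necessarily make a successful intervention look harmful. The document does not support a fixed direction. It says nothing about how the teeth of prompted attenders compare with those of habitual attenders. If prompted users are former non-attenders with neglected teeth, the bias looks like harm. If control users attend mainly because of symptoms, prompted routine attenders could have better teeth, and the bias would favour the intervention.

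**Conclusion.** The point holds for the optional DMFT denominator. On the described source, a DMFT contrast would be conditioned on the primary outcome and would not compare the randomised groups. Its bias is the prompted share of intervention-arm attenders multiplied by their DMFT gap from habitual attenders: about ±1.5 points on about 2.5 against 10 records at 5%/20%, and about ±0.6 on 17.5 against 25 records at 35%/50%. These sizes rest on an equal split, full consent, attendance never being reduced by the intervention, and a 2-point gap chosen for illustration. The selection itself needs no gap to be assumed; only its size and sign do. The insensitivity of a summed DMFT to treatment is an additional reason against it. The matter is confined to an optional part of the economic evaluation and leaves the primary analysis untouched, but it should be corrected because the plan allows a biased estimate for which it already has a better alternative.

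**What to change.** In Health economic analysis, delete the parenthesis "or Decayed, Missing and Filled Teeth (DMFT) rates if available", so that kept appointments or dental visits are the only effectiveness denominator. Add one sentence there: clinical state supplied by dentists will be described among attenders only, without comparison between arms and without any inference about the effect on oral health. The dentists' records remain useful for confirming visits and costing the treatment given, and the Follow-up procedure need not change.

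The cost is a change of wording. The sponsor gives up an optional DMFT-based ICER; the first-named denominator and the visit data remain. The remedy is the same whichever way the bias would run.

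### The probabilistic sensitivity analysis is to yield a range of ICERs, which loses its meaning if simulated effect differences cross zero, as they can on the 100-person subsample

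*Protocol article*

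**What the plan says.** All of this is in the protocol article. Health economic analysis states the purpose of the probabilistic sensitivity analysis: "a detailed probabilistic sensitivity analysis will be carried out in order to get a range of incremental cost-effectiveness ratios". For the ratio itself, "the denominator would be patients keeping their dental appointments during the year", with DMFT rates as an alternative if they become available.

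On the source of the effect, the same section says "Data regarding dental visits from a subsample of 100 service users will be obtained at the end of the study period" and that "the difference in dental visits between the two groups can be used in calculation of the incremental cost-effectiveness ratio". Follow-up describes how the subsample is formed: "A total of 100 service users will be randomly selected from all teams". Each person is first asked whether contact is acceptable, and "If it is not - no contact will be made".

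The full evaluation is conditional: "Should there be a statistically significant difference between the two groups, we would proceed with a full economic evaluation". If there is no difference, only a cost analysis follows.

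**The concern.** An ICER is a cost difference divided by an effect difference, so it is discontinuous where the effect difference is zero. Just above zero it is very large and positive. Just below zero, with a positive cost difference, it is very large and negative. A negative value arises in two opposite cases: the intervention costs less and works better, or it costs more and works worse. Sorting the draws to obtain a range places both below every positive ratio.

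Health economic analysis expects added training, staff time and dental appointments, so negative ratios would come mostly from draws in which the intervention is dominated. A reader who sees a negative lower limit would be likely to take it as possible cost saving, when it means the reverse. What is at stake is how the uncertainty about cost-effectiveness is reported. The primary comparison is not affected.

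**Working it through.** **Inputs from the protocol article.** Sample size, Table 1: "Sample size needed to detect an absolute difference of 15% in the proportion of visits to a dentist", with control rates of 5% to 35%, α 5% and power 80%; ICC 0.1; 10 patients per staff member. Abstract: 10 teams, five per arm. Health economic analysis and Follow-up: subsample of 100.

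**Assumptions.** The 100 split 50/50 by arm and all respond. The Table 1 proportions stand for the ICER denominator. Draws are normal. No DMFT figures are given, so that alternative cannot be checked.

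**The plan's own figure.** For 5% vs 20%, the two-sided two-proportion formula with continuity correction gives 88 per arm, 176 in total. Then 176 × 1.9 = 334.4 (stated 334) and 334 / 0.8 = 417.5 (stated 418). The other non-cluster totals in Table 1 also reproduce, so these inputs are read as the protocol used them.

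**Design effect (DE) in the subsample.** Two readings are defensible:
- Team-level clustering: 100 / 10 teams = 10 per team, so DE = 1 + (10 − 1) × 0.1 = 1.9.
- Co-ordinator-level clustering: Trial status gives 1,074 service users, and at 10 per co-ordinator that is about 107 co-ordinators. A random 100 is then about one each, so DE is near 1.0.

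**Share of draws below zero.** SE = √(DE × [p₁(1 − p₁) + p₂(1 − p₂)] / 50), and the share is Φ(−0.15 / SE), with draws centred on the true 15 points.

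| Rates | Variance sum | SE, DE 1.0 | Share below 0 | SE, DE 1.9 | Share below 0 |
|---|---|---|---|---|---|
| 5 vs 20% | 0.2075 | 0.0644 | 1.0% | 0.0888 | 4.6% |
| 20 vs 35% | 0.3875 | 0.0880 | 4.4% | 0.1213 | 10.8% |
| 35 vs 50% | 0.4775 | 0.0977 | 6.2% | 0.1347 | 13.3% |

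With 40 per arm (20% non-response, borrowing the protocol's dropout rate) the shares are 1.9–8.5% and 6.5–16.0%.

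**What an actual analysis would show.** Real draws centre on the observed estimate. If every draw costs more, the lower 95% limit is negative once over 2.5% of draws fall below zero, that is, when the estimate is under 1.96 SE. Ignoring the significance condition, that probability is Φ(1.96 − 0.15 / SE): 36% to 66% at DE 1.0 and 61% to 80% at DE 1.9, across Table 1.

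**Effect of the significance condition.**
- Same data for test and ICER: significance in favour of the intervention means an estimate above 1.96 SE, so fewer than Φ(−1.96) = 2.5% of draws lie below zero and the negative limit does not arise.
- Test on the main data, ICER on the subsample: simulated with 350 per arm (half of 700, the midpoint of the 600–800 checklists under Data analysis, treated here as people) and 50 per arm nested inside. Among trials that pass, the subsample's 95% range still straddles zero in about a third to two thirds without clustering, rising with the control rate. With a team ICC of 0.1 it does so in about a third to a half, depending on how test and interval are computed.

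**Monetary illustration (assumed costs; none are in the protocol).** With an extra cost of GBP 30 (SD 5) per user and 5 vs 20%, the point ICER is 30 / 0.15 = GBP 200. The 95% percentile range is about −940 to 1,520 at DE 1.9, but about 89 to 902 at DE 1.0. At 35 vs 50% the lower limit is negative either way (about −1,220 at DE 1.0). The outer limits shift somewhat between simulation runs.

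**The case against.** The strongest objection is the significance condition: no ICER is planned unless the groups differ. This holds fully when the test and the ICER share their effect data. It also disposes of a tempting extension to the whole cohort with a large team-level design effect. In that setting, results with more than 2.5% of draws below zero are the ones that fail the condition, so no ICER range would be reported for them.

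Second, use of the subsample is permitted, not fixed. The primary outcome is collected by checklist. If 600–800 checklists supplied the effect at the protocol's design effect of 1.9, fewer than 0.4% of draws would fall below zero. A reader might infer that the ICER must rest on the 100; the text does not say so. It is, however, the one source that the section names for the visit difference in the ratio.

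Third, a reader might infer that the range is the sole planned statement of uncertainty. The article names no other, but it is a condensed text and excludes none. Nor does it say whether the range is a percentile interval or a minimum and maximum. This lowers the weight of the point without removing it, because the summary that is named is the unsound one.

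Fourth, 5–13% could be read as a property of the plan. It is not: it depends on an equal split, full response and DE 1.9, none of which the protocol states for the subsample.

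**Conclusion.** The point holds as a minor one. The stated output cannot be interpreted when effect draws cross zero. On the subsample, under a true 15-point effect and 50 complete responses per arm, about 1–6% of draws do so at DE 1.0 and about 5–13% at DE 1.9. Refusals would raise these shares.

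The exposure is conditional. It is essentially absent if one dataset serves both the significance test and the ICER. It is material, at roughly a third to two thirds of trials that pass, if the test uses the main data and the ICER uses the subsample. The article leaves open which of these applies. The monetary figures only illustrate the mechanism, and at low attendance rates the sign of the lower limit depends on the design effect.

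**What to change.** In Health economic analysis, replace the range of ICERs as the output of the probabilistic sensitivity analysis with:

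- incremental cost and incremental effect, each with an interval;
- the joint draws on the cost-effectiveness plane;
- net monetary benefit with a cost-effectiveness acceptability curve, over a stated range of values per additional attender;
- the ICER as a point estimate only.

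Generate the draws so that they respect team clustering, for example by resampling teams or from a team-level bivariate model of cost and effect. It would also help to state whether the effect comes from the checklists or the subsample, since the size of the problem turns on that.

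The cost is small: a change of wording, with the same data and essentially the same simulation. The downside is slightly more reporting and the need to state a range of values per additional attender.
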